### MRI image acquisition

Imaging is conducted on a 3T Siemens Magnetom Prisma scanner (Siemens Healthineers, Erlangen, Germany) at the University of Regensburg using a 64-channel head/neck coil. rsFC is acquired before and after stress induction via MIST using a multi-band EPI sequence (470 volumes, 48 slices with isotropic voxel size of 2.5 × 2.5 × 2.5 mm³, 240 × 240 mm² FOV, TR = 1000 ms, TE = 30 ms, flig angle (FA) = 59° and multiband factor = 4 resulting in a total scan time of 8 min). Task-based fMRI uses a separate EPI sequence (233 volumes, 60 slices with isotropic voxel size of 2.5 × 2.5 × 2.5 mm³, 240 × 240 mm² FOV, TR = 2000 ms, TE = 30 ms and multiband factor = 4 resulting in a total scan time of 8 min). A gradient echo field mapping sequence (50 slices, isotropic voxel size of 2.0 × 2.0 × 2.0 mm³, 220 × 220 mm² FOV, TR = 645 ms, TE1 = 4.92 ms, TE2 = 7.38 ms resulting in a total scan time of 2 min and 27 s) is used to estimate B_0_ field inhomogeneities. Diffusion-weighted imaging is performed using a multi-band EPI sequence (72 slices with isotropic voxel size of 2.0 × 2.0 × 2.0 mm³, 212 × 212 mm² FOV, TR = 3900 ms, TE = 78.2 ms, diffusion weighting b = 2000 s/mm² applied along 136 noncollinear directions, including non–diffusion-weighted (b = 0) images acquired for reference and multiband factor = 2 resulting in a total scan time of 9 min and 33 s). High-resolution T1-weighted structural images are acquired using a Magnetization Prepared Rapid Acquisition Gradient Echo (MPRAGE) sequence (192 slices with isotropic voxel size of 0.9 × 0.9 × 0.9 mm³, 240 × 240 mm² FOV, TR = 2300 ms, TE = 2.32 ms, inversion time (TI) = 900 ms, FA = 8° resulting in a total scan time of 5 min and 21 s). T2-weighted structural images are acquired using a Fluid-Attenuated Inversion Recovery (FLAIR) sequence (26 slices with isotropic voxel size of 0.9 × 0.9 × 5.0 mm³, 230 × 230 mm² FOV, TR = 10000 ms, TE = 96 ms, TI = 2500 ms, FA = 150° resulting in a total scan time of 2 min and 42 s).

### MRI preprocessing

MRI data will be preprocessed using fMRIPrep [85, 86], a standardized pipeline that integrates best practices and ensures reproducibility. T1-weighted structural images will be skull-stripped and segmented into gray matter, white matter, and cerebrospinal fluid. Functional images will be corrected for head motion and slice-timing effects, and subsequently normalized to the MNI NIH Pediatric Asym template (Cohort 6, ages 13–18) [87, 88], which provides age-appropriate anatomical reference data for adolescent populations. Although fMRIPrep also produces derivatives in standard adult MNI space (MNI152NLin6Asym), all planned analyses will be conducted in the pediatric template space, with ROI (region-of-interest) masks coregistered accordingly.

### MRI and statistical analysis

In accordance with the preregistered clinical trial protocol (DRKS00032507), two primary outcome domains were originally defined: MRI measures and neuroendocrine responses. In the present manuscript, we focus primarily on rsFC within the fronto-limbic network and hormonal reactivity as the main outcomes. Some secondary outcomes specified in the DRKS protocol (e.g., psychological assessments) will be reported elsewhere. These deviations reflect updated hypotheses and advances in the field since the trial registration.

#### Primary outcomes

The first primary outcome is rsFC. We hypothesize that time (pre- vs. post-stress) × group (MDD, COM, HC) interactions will be observed in fronto-limbic connectivity.

Six a priori fronto-limbic ROIs will be examined: bilateral amygdala, hippocampus, ACC, insula, dorsolateral prefrontal cortex (dlPFC), and ventromedial prefrontal cortex (vmPFC), defined using the Harvard–Oxford cortical and subcortical atlases as implemented in the CONN toolbox [89]. This yields 15 possible pairwise connections. For each subject, mean time series will be extracted from each ROI, pairwise Pearson correlations will be computed, and coefficients will be Fisher’s z-transformed to normalize distributions. Group differences will be assessed using general linear models (GLMs) with time (pre- vs. post-stress) as within-subject factor and group (MDD, COM, HC) as between-subject factor. Sex assigned at birth, age, pubertal status (linear and quadratic terms), and medication status (yes/no) will be included as covariates. Additional psychiatric comorbidities (e.g., ADHD, OCD, PTSD, eating disorders) will be recorded but not included as routine covariates due to diagnostic heterogeneity and low subgroup frequencies; however, planned sensitivity analyses will be conducted excluding participants with additional comorbid diagnoses to assess robustness of findings. Due to the expected small number of left-handed participants, groups will not be matched on handedness; however, EHI scores will be considered as covariates in rsFC analyses. False Discovery Rate (FDR) correction across the 15 tested edges will be applied.

Exploratory analyses will extend this approach to a broader corticolimbic network comprising 25 ROIs previously identified as part of stress-sensitive circuitry [90–92]. For each ROI, the average time series will be extracted and rsFC estimated via Pearson correlations and Fisher’s z-transformation. The resulting z-values will serve as edge weights for subsequent network analyses. Multiple comparisons will be controlled using FDR correction across the 300 tested pairwise connections. In addition to the predefined ROI-to-ROI analyses, we will conduct exploratory, hypothesis-generating analyses to characterize stress-related changes in whole-brain connectivity. Specifically, each of the six a priori ROIs (bilateral amygdala, hippocampus, ACC, insula, dlPFC, vmPFC) will be used as seeds in seed-to-voxel analyses. rsFC will be estimated with all other voxels across the brain to identify potential alterations beyond the predefined corticolimbic circuitry. While these analyses are not restricted to predefined networks, particular attention will be paid to connectivity patterns involving large-scale systems, including the default mode, salience, and fronto-parietal networks, as defined by the Yeo 7-network parcellation and the Harvard–Oxford cortical and subcortical atlases. Multiple-comparison correction will be applied using FDR within each seed analysis. Primary analyses (fronto-limbic rsFC and hormonal reactivity) are treated as separate preregistered outcome domains and are each corrected using FDR procedures. Exploratory ROI-to-ROI and seed-to-voxel analyses are explicitly defined as hypothesis-generating and interpreted with caution, with FDR correction applied within each analytic family. This approach controls Type I error inflation while allowing exploratory analyses to inform future hypothesis development. This exploratory approach reflects the limited prior evidence in adolescent samples [92] and aims to generate hypotheses for future targeted studies.

The second primary outcome is hormonal reactivity. We hypothesize that stress exposure will elicit group differences in OXT, CORT and sAA. Raw hormonal values will be square-root transformed to reduce skewness [93]. Reactivity will be quantified using area under the curve (AUC) [94] with respect to increase (AUC_i_) and ground (AUC_g_), as well as delta scores reflecting change from baseline to peak, peak to recovery, and recovery magnitude [95–97]. Repeated-measures ANOVAs will examine the interaction between time (baseline, peak, recovery; within-subject factor) and group (between-subject factor), controlling for sex, age, and pubertal status. False Discovery Rate (FDR) correction will be applied across hormonal outcomes and indices. Subjective stress ratings assessed with VAS will be analysed in parallel, using repeated-measures ANOVAs with the same model structure.

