### Sample size and power analysis

An a-priori power analysis was carried out with G*Power 3.1 [39]. We modelled a one-way fixed-effects Analysis of Variance (ANOVA) with three independent groups (healthy controls [HC], major depressive disorder [MDD], and MDD with comorbid anxiety [COM]).

Previous rsFC studies in adolescents with MDD report medium to large effect sizes. Connolly et al. [40] demonstrated reduced amygdala–prefrontal rsFC in adolescents with MDD compared to controls (medium effect; *d* ≈ 0.4–0.6), although numerical effect sizes were not directly reported. Cullen et al. [41] reported group differences in amygdala–prefrontal connectivity that, when derived from published means and standard deviations, correspond to large effects (*d* ≈ 1.0–1.3).

Assuming α = 0.05 (two-tailed) and a desired power of 1-*β* = 0.80, the analysis indicated a required total sample size of *N* = 84 (28 per group). To account for potential data loss due to head motion or dropout, we plan to include *N* = 90 participants, i.e. 30 per group.

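### The primary rsFC time × group model lists only covariates that are constant across the two rest scans and no head-motion term, so residual motion that changes differently by group can bias the interaction

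*Protocol article*

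**What the plan says.** Under Primary outcomes, the protocol article states the hypothesis as an interaction: "We hypothesize that time (pre- vs. post-stress) × group (MDD, COM, HC) interactions will be observed in fronto-limbic connectivity". The outcome for each edge is built as follows: "mean time series will be extracted from each ROI, pairwise Pearson correlations will be computed, and coefficients will be Fisher’s z-transformed to normalize distributions". The model is then given, down to its group term: "Group differences will be assessed using general linear models (GLMs) with time (pre- vs. post-stress) as within-subject factor and group (MDD, COM, HC) as between-subject". Its adjustment is spelled out as far as a squared term: "Sex assigned at birth, age, pubertal status (linear and quadratic terms), and medication status (yes/no) will be included as covariates". The same paragraph adds that "EHI scores will be considered as covariates in rsFC analyses", explains why additional psychiatric comorbidities are not routine covariates, and applies FDR across the 15 edges.

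Head motion appears in two other places. Under MRI preprocessing: "Functional images will be corrected for head motion and slice-timing effects". Under Sample size and power analysis, the increase from 84 to 90 participants is an allowance for "potential data loss due to head motion or dropout".

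**The concern.** With two scans per person, the time × group test is a comparison of post-minus-pre change between groups. A nuisance variable threatens that comparison if it changes between the scans by a different amount in different groups and is related to connectivity. Sex, age, pubertal status, medication and handedness do not change within a session. They can absorb only whatever part of a motion change they happen to predict.

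Head motion can change within a session, and the design makes a differential change plausible. The post-stress scan always comes after the stress task and after more time in the scanner. The study's premise is that the groups react differently to that stressor. Patients may carry comorbidities such as ADHD that are recorded but not modelled, whereas controls may have no current or past psychiatric disorder.

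Image-level motion correction does not adjust the Fisher-z edges for whatever motion effect remains. What is at stake is interpretation: part of a difference in motion could be read as stress-related change in connectivity. FDR limits false discoveries that arise by chance. It does not remove a bias in the estimates being tested.

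**Working it through.** The article states no figure for this point, so there is nothing of its own to reproduce. The check asks how far the nominal 5% error could move.

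**Inputs from the article.** Three groups; 28 per group (84) required and 30 per group (90) planned; two rest scans; α = 0.05 two-tailed.

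**Assumptions (not in the documents).** *r* is the within-group correlation between motion change and connectivity change on an edge, taken as 0.1 to 0.3. Δ is the difference in motion change between each clinical group and controls, in SD units, taken as 0.3 to 0.5. There is no true group effect on connectivity change.

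**Step 1: bias.** The spurious difference in connectivity change is *b* = *r* × Δ.
- Low end: 0.1 × 0.3 = 0.03 SD
- High end: 0.3 × 0.5 = 0.15 SD

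**Step 2: three-group interaction, 30 per group.** If both clinical groups are shifted by *b* relative to controls, the variance of the three group means is 2*b*²/9. The noncentrality of the F test with 2 and 87 df is therefore λ = 90 × 2*b*²/9 = 20*b*².

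| *r* | Δ | *b* | λ | Rejection rate under the null |
|---|---|---|---|---|
| 0.1 | 0.3 | 0.03 | 0.018 | 5.1% |
| 0.2 | 0.3 | 0.06 | 0.072 | 5.5% |
| 0.2 | 0.5 | 0.10 | 0.200 | 6.5% |
| 0.3 | 0.3 | 0.09 | 0.162 | 6.2% |
| 0.3 | 0.5 | 0.15 | 0.450 | 8.4% |

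**Step 3: pooled patient–control contrast, 56 against 28.** The noncentrality is *b* × √(56 × 28/84) = 4.32*b*, and the rejection rate is P(|Z + 4.32*b*| > 1.96).
- *b* = 0.03: noncentrality 0.13, rate about 5.2%
- *b* = 0.15: noncentrality 0.65, rate about 9.9%

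**Step 4: does the remedy work?** The three-group test was simulated with 30 per group and 4,000 runs per setting, with motion change added as a covariate. For *r* = 0.2 and 0.3 with Δ = 0.3 and 0.5, the rejection rate was 5.0% to 5.6%, close to nominal. If *r* or Δ is zero, nothing is inflated even without the covariate.

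**Step 5: beyond the assumed range.** The rate grows if either assumption is pushed further. At *r* = 0.4 and Δ = 0.8 the unadjusted three-group test rejects 22% of the time. Nothing in the documents points to values that large, so the conclusion does not use that figure.

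**The case against.** The strongest reply is that this is a condensed article. Confound regression, censoring and motion exclusion limits are commonly left to a fuller document, and the article names both fMRIPrep and the CONN toolbox. How much motion reaches the Fisher-z edges depends on that unseen denoising. This stands as a limit on size, and the absence of denoising detail is not the point here. The point is the group-level model, whose covariates the article does state.

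A second reply is that the list may not be closed. Handedness is to be considered, and the Eligibility criteria section says contraceptive use will be corrected for, yet contraceptive use is not in the covariate sentence. This also stands: the sentence does not prove that motion is ruled out. But the additions are again fixed across the two scans, and none is a motion measure.

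A third reply is that motion may itself result from stress or diagnosis, so adjusting for it could remove part of the effect under study. That is right, and it argues for showing both results.

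A reader might also infer three stronger things that the documents do not support:
- That motion is the only nuisance variable that can change between scans. Arousal, breathing and drowsiness can change too.
- That residual motion moves many edges in the same direction. Nothing in the article shows this, and the FDR argument does not need it.
- That the plan ignores motion. It corrects the images and allows for lost scans.

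**Conclusion.** The concern holds at a modest size. The covariates stated for the primary rsFC interaction cannot represent a nuisance that changes between the two scans, and motion is a plausible one. Under the assumed ranges the nominal 5% error per edge becomes about 5–8% on the planned three-group interaction and about 5–10% on a pooled patient–control contrast. At the low end the inflation is negligible, and effective first-level denoising would reduce it throughout. The result depends on two quantities that the documents do not give: the relation of residual motion to connectivity, and the group difference in motion change. The documents do not show that such a difference exists. The change is worth making because it costs almost nothing, and fixing it before analysis avoids a choice made after seeing the results.

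**What to change.** In the primary rsFC model under Primary outcomes, and in the exploratory 25-region and seed-to-voxel rsFC models in the same section, add mean framewise displacement of each rest scan, computed from the existing preprocessing. It must be scan-specific: a time-varying covariate or, in the change-score form, its pre-to-post change. A single session average entered as a main effect would not adjust the interaction.

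State that the time × group result will be reported with and without this term, and give the reason. Report motion by group and scan beside the primary result.

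The cost is a short addition to the text, about one degree of freedom and one extra model run. No new data are needed.

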Further, using Visual Analogue Scales (VAS) [75] (1 = “not at all”; 10 = “extremely”) participants are asked about how stressed, anxious, angry, ashamed, and guilty they feel at nine different time points throughout T2 (see Fig. 3). VAS are particularly suitable for assessing subjectively experienced stress, as they have been shown to be both reliable [76] and valid [77].

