#### Saliva sampling

To analyse peripheral OXT, CORT and sAA levels, saliva samples are collected at eight time points using Salivettes^®^ (Sarstedt, Nümbrecht, Germany; item number 51.1534.500) following a standardized protocol [78]. Samples are stored at -20 °C until biochemical analysis. Salivary OXT will be analysed by radioimmunoassay (RIAgnosis, Sinzing, Germany). Salivary CORT and sAA will be quantified at the Department of Biopsychology, Technical University of Dresden, Germany.

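### The hormone time × group test uses three time levels although eight saliva samples are taken; a mixed model on all available samples is a cheap improvement

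*Protocol article*

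**What the plan says.** Under Primary outcomes, the protocol article gives one time × group test for OXT, CORT and sAA: "Repeated-measures ANOVAs will examine the interaction between time (baseline, peak, recovery; within-subject factor) and group (between-subject factor"), with adjustment described as "controlling for sex, age, and pubertal status". The same paragraph also plans summary indices: "Reactivity will be quantified using area under the curve (AUC) [94] with respect to increase" and to ground, and "delta scores reflecting change from baseline to peak, peak to recovery, and recovery magnitude". FDR correction runs across hormones and indices.

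Under Saliva sampling, "saliva samples are collected at eight time points". For the subjective ratings, Primary outcomes says: "Subjective stress ratings assessed with VAS will be analysed in parallel, using repeated-measures ANOVAs with the same model structure". Psychological measures places these ratings at "nine different time points throughout T2".

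The text shown does not tie baseline, peak and recovery to particular samples. Fig. 3, which illustrates the T2 procedure, is not visible here and may do so.

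**The concern.** The stated model has three time levels for a primary outcome measured eight times, and for ratings measured nine times. A classical repeated-measures ANOVA works on one row per participant with a value in every level. A participant who lacks one of those values leaves the analysis, and their remaining samples go unused. Samples outside the three levels can neither help to estimate the contrasts nor stand in for a missing value. The AUC indices do not repair this: an AUC built from the full series has more values that can be missing.

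At stake is some power on a primary outcome. The ANOVA also generally needs a stronger assumption about missing samples than a likelihood model, which is valid if missingness depends only on observed data.

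**Working it through.** The plan gives no figure to reproduce on this point. Its only sample-size calculation concerns a one-way ANOVA supported by rsFC effect sizes and contains no hormone quantity.

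**Inputs.** Eight samples per participant (Saliva sampling); three time levels (Primary outcomes); 90 participants, 30 per group (Sample size and power analysis). The missing rate per sample, m, is not given. I assume 2%, 5% and 10%, independent between samples.

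**Samples in the ANOVA.** If each level is one sample, the time factor uses 3/8 = 37.5% of them: 90 × 3 = 270 of 90 × 8 = 720.

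**Participants kept.** The expected share is (1 − m)^3 for the three-level ANOVA and (1 − m)^8 for a full-series AUC.

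| m | (1 − m)^3 | of 90 | (1 − m)^8 | of 90 |
|---|---|---|---|---|
| 2% | 0.941 | about 85 | 0.851 | about 77 |
| 5% | 0.857 | about 77 | 0.663 | about 60 |
| 10% | 0.729 | about 66 | 0.430 | about 39 |

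A mixed model keeps every participant with at least one value.

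**Power for the same contrasts.** The article gives no hormone SD or within-person correlation, so the gain can only be simulated under assumptions. Two simulations with 30 per group compared complete cases on three samples with an unstructured likelihood model on all eight, testing the same baseline, peak and recovery contrasts. Simulation A used a shared subject component of 0.5 plus an AR(0.5) residual, a rise-and-fall response, a peak 0.6 SD smaller in patients, and 800 runs. Simulation B used a sharply peaked response.

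| m | A: mixed vs ANOVA | B: mixed vs ANOVA |
|---|---|---|
| 2% | 78% vs 78% | 73% vs 71% |
| 5% | 79% vs 72% | 70% vs 63% |
| 10% | 78% vs 66% | 73% vs 62% |

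The gains are 0 to 2, 7, and 11 to 12 points. With 800 runs, the simulation error on one power figure is about √(0.75 × 0.25 / 800) = 0.015, or 1.5 points, so the difference at 2% is negligible. Type I error was 5–6% (mixed) against 4–6% (ANOVA) in A, and 4–5% for both in B.

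**Should the eight samples be pooled into phases?** No. Power for phase averages against three single samples, at 2% missing, depended on the shape of the response:
- blunting at the peak sample, 40% as large at its neighbours: 51% vs 73%;
- blunting 60% as large at the neighbours: 73% vs 73%;
- equal blunting across the peak phase: 96% vs 72%.

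Pooling can dilute a sharp peak, so the gain quoted here is for a model that keeps sample number as the time factor.

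**The case against.** The strongest reply is that a three-level repeated-measures ANOVA beside AUC and delta scores is a conventional and valid choice, and that with few missing samples almost nothing is lost. That stands: at 2% missing the gain is 0 to 2 points. T2 is also a single session of about 2.5 hours, so gaps may be rare.

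Four stronger readings are tempting, and the documents do not support them.
- A reader might infer that the plan prescribes complete-case analysis. It does not say so. Deletion follows from how the named method is normally fitted, and a rule for missing samples may stand in an analysis plan not shown. The absence of such a rule is not part of this point.
- A reader might infer that most samples are discarded. That applies at most to the ANOVA's time factor. AUC belongs to the same primary outcome and would normally use the full series, and the text shown does not say that each level is a single sample.
- A reader might infer that the result will be biased because distressed patients lose more samples. This is plausible in a stress experiment, but the article offers no evidence for it.
- A reader might infer that the step from 84 to 90 leaves the hormone test a reserve of only six. That allowance concerns head motion and dropout in a calculation based on rsFC, so it measures no margin for hormones.

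**Conclusion.** The point holds as a cheap improvement to a stated analysis choice, not as an error. The ANOVA is valid, but as normally fitted it uses less of the collected data than a mixed model would and loses participants who lack a required value. The size rests on the assumed missing rate, independence between samples and the simulated covariance: negligible power gain at 2% missing, about 7 points at 5%, and 11 to 12 at 10%. A full-series AUC is more exposed to gaps than the ANOVA, with about 85%, 66% and 43% of participants complete at those rates.

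**What to change.** Replace the three-level ANOVA with a linear mixed model for each hormone:
- Fit all available samples by REML, with Kenward-Roger or Satterthwaite degrees of freedom.
- Use sample number as a categorical time factor, crossed with group. Do not pool samples into phases.
- Use an unstructured covariance or a pre-specified serial one. Unstructured means 8 × 9 / 2 = 36 parameters for saliva and 9 × 10 / 2 = 45 for VAS, so name a fallback in case the fit does not converge.
- Fix, for each hormone and before data are seen, which sample numbers are baseline, peak and recovery, and test group differences in those contrasts.
- Keep the planned covariates.
- Derive AUC contrasts from the fitted means, or impute missing samples before computing AUC.
- Use the same approach for the nine VAS ratings.

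The cost is some model wording, a covariance choice made in advance and a little more analysis work. No extra data are needed, and SPSS, already named in the article, fits mixed models.

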### Hypotheses

We expect blunted CORT and OXT stress responses in adolescents with MDD (with or without comorbid anxiety) relative to healthy controls, whereas baseline levels of these hormones are not expected to differ systematically across groups. For rsFC, we hypothesize time (pre- vs. post-stress) × group (MDD, COM, HC) interactions within fronto-limbic circuits, with greater alterations in adolescents with depressive disorders compared to healthy controls. Exploratorily, we expect that youth with MDD and comorbid anxiety will show more pronounced endocrine blunting and stronger fronto-limbic rsFC alterations than those with MDD alone. Finally, we hypothesize that stress-induced fronto-limbic rsFC changes will be significantly associated with endocrine reactivity (CORT, OXT, sAA), reflecting shared neuroendocrine mechanisms of stress adaptation.

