### Eligibility criteria

Eligibility is initially assessed via telephone screening and confirmed at the first study appointment. Participants must be adolescents aged 12–17 years. For the clinical groups, inclusion requires a primary diagnosis of at least moderate depression; the comorbid group additionally requires an anxiety disorder diagnosis. In case of discrepancy between clinical diagnoses and the results according to the structured clinical interview M.I.N.I.-KID, final group assignment is determined through expert consensus. Psychotropic medication and hormonal contraceptives are noted and will be corrected for but are not exclusion criteria. Full inclusion and exclusion criteria are listed in Table 1.

**Table 1 Tab1:** Inclusion and exclusion criteria

**Inclusion Criteria**	**General:** • Adolescents aged 12–17 years • Sufficient understanding of the German language • Written informed consent from participant and legal guardian
	**Depressive Group**: Primary diagnosis of depressive disorders: • Moderate depressive episode (F32.1) • Severe depressive episode without psychotic symptoms (F32.2) • Severe depressive episode with psychotic symptoms (F32.3) • Major depressive disorder, recurrent, moderate (F33.1) • Major depressive disorder, recurrent, severe without psychotic symptoms (F33.2) • Depressive disorder, recurrent, severe with psychotic symptoms (F33.3)
	**Comorbid Group**: Primary diagnosis of depressive disorders and an additional anxiety disorder: • Agoraphobia with/without panic disorder (F40.00/F40.01) • Social phobia (F40.1) • Panic disorder (F41.0) • Generalized anxiety disorder (F41.1) • Separation anxiety disorder of childhood (F93.0) • Social anxiety disorder of childhood (F93.2) • Generalized anxiety disorder of childhood (F93.80)
	**Control Group**: Matched by sex and age; school type, handedness, pubertal status, contraceptive intake are controlled for
**Exclusion Criteria**	**General**: • Pregnancy/lactation • Pubertas praecox vera • Acute suicidal behavior • Glucocorticoid-containing medication • Genetic syndromes • Traumatic brain injury • Endocrinological or immune disorders • Chronic neurological disorders affecting brain development and physiology
	**Cognitive/Developmental**: • Intellectual impairment (IQ < 80) • Attendance at a school for special needs
	**MRI-Specific**: • Metallic foreign bodies (e.g., braces, cochlear implants, non-removable piercings) • Upper-body tattoos • Claustrophobia

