	**Psychiatric Disorders**: Current/past diagnosis of: • Psychotic disorders • Autism • Bipolar disorder • Mental and behavioural disorders due to psychoactive substance use • Anorexia nervosa (if BMI < 16,5)
	**Control Group-Specific**: • Current or past psychiatric disorders • In-/outpatient psychiatric or psychotherapeutic treatment

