#### Physiological consistency of measurement

All measurements are conducted on weekdays, with the experimental session (T2) scheduled exclusively in the afternoon to minimize circadian influences on hormone levels [79, 80]. For post-menarcheal females not using contraceptives, T2 is scheduled during the luteal phase (estimated based on self-reported cycle length, menstruation duration, and the date of last menstrual onset) to ensure comparability of CORT reactivity across sexes [81, 82]. Although no significant sex differences in OXT levels have been reported in adolescents [83], oral contraceptive use is assessed and statistically controlled, given evidence that such use blunts CORT reactivity [84]. Participants are instructed to refrain from eating and to only drink water two hours before and during T2, with compliance confirmed via self-report.

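### The primary hormone model omits contraceptive use, which the protocol says is statistically controlled, and leaves open how psychotropic medication is handled

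*Protocol article*

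**What the plan says.** Two sections of the protocol article commit to adjustment. Eligibility criteria: "Psychotropic medication and hormonal contraceptives are noted and will be corrected for but are not exclusion criteria". Physiological consistency of measurement: "oral contraceptive use is assessed and statistically controlled, given evidence that such use blunts CORT reactivity". Table 1, in the row for the control group, adds: "Matched by sex and age; school type, handedness, pubertal status, contraceptive intake are controlled for".

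The analysis text for the second primary outcome (Primary outcomes) then names its covariates. The OXT, CORT and sAA models are repeated-measures ANOVAs of time (baseline, peak, recovery) "and group (between-subject factor), controlling for sex, age, and pubertal status". Neither contraceptive use nor medication is listed.

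For the first primary outcome, resting-state connectivity, the same section gives a different list: "Sex assigned at birth, age, pubertal status (linear and quadratic terms), and medication status (yes/no) will be included as covariates".

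The endocrine hypothesis (Hypotheses) reads: "We expect blunted CORT and OXT stress responses in adolescents with MDD (with or without comorbid anxiety) relative to healthy controls". Table 1 excludes controls with "In-/outpatient psychiatric or psychotherapeutic treatment".

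**The concern.** The protocol names a factor that blunts cortisol reactivity, promises to adjust for it, and then specifies a primary cortisol model without it. The effect it attributes to contraceptives has the same sign as the effect it hypothesises for the disease.

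The design does not close the gap. Contraceptive users are not excluded, only sex and age are matched, and luteal-phase scheduling applies only to post-menarcheal females who do not use contraceptives. Sex, age and pubertal status absorb only the part of contraceptive use that they predict. A remaining imbalance between patients and controls would go into the group comparison.

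There is also a question of prespecification. An analyst who follows Physiological consistency of measurement and one who follows Primary outcomes would fit different primary models. If the choice is made after the hormone data are seen, it is no longer prespecified.

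Psychotropic medication has the same textual gap but a different structure. Controls may not be in psychiatric treatment, so medication falls almost only in the two patient groups.

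**Working it through.** **Step 1. Covariates by model** (Primary outcomes and Secondary outcomes)

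| Model | Demographic and pubertal terms | Medication | Contraceptives |
|---|---|---|---|
| rsFC, primary | sex, age, puberty (linear, quadratic) | yes | no |
| OXT/CORT/sAA, primary | sex, age, puberty | no | no |
| Structural MRI | sex, age, puberty | no | no |
| DTI | sex, age or puberty | yes | no |
| Task fMRI | sex, age or puberty | yes | no |
| Regressions for CORT increase and CORT recovery | none | no | no |

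Contraceptive use appears in no row. Medication appears in three imaging models and in no hormone model. The sensitivity and exploratory analyses described (additional comorbidity, symptom scores, group × sex) do not bring either variable in.

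**Step 2. Size of the possible bias.** The plan gives no figure to reproduce, and the documents give neither contraceptive prevalence by group nor the size of the blunting. The inputs below are assumptions.

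Bias in the patient-control difference = Δp × b, where Δp is the difference in contraceptive prevalence left after sex, age and pubertal status, and b is the blunting in SD units.

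- Low end: 0.1 × 0.5 = 0.05 SD
- High end: 0.3 × 1.0 = 0.30 SD
- Balanced use: 0 × b = 0

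The sign follows Δp. Higher use in patients imitates the hypothesised blunting; higher use in controls masks it.

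**Step 3. Effect on the test.** This was simulated with 30 per group, no disease effect, 70% female, contraceptive use of 10% among female controls and 30% to 50% among female patients, and 4,000 runs per setting. The outcome was a single reactivity score with within-group SD 1, tested with a 2-df group F-test at 5%, adjusted for sex and age. Everything except the 30 per group and the 5% level is assumed. It is a simplification of the repeated-measures design.

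| Blunting b | Use in female patients | Expected bias, b × 0.7 × (difference among females) | Type I error, no contraceptive term | Type I error, with term |
|---|---|---|---|---|
| 0.5 SD | 30% | 0.5 × 0.7 × 0.2 = 0.07 SD | 5.8% | 4.8% |
| 0.5 SD | 50% | 0.5 × 0.7 × 0.4 = 0.14 SD | 7.7% | 4.8% |
| 1.0 SD | 30% | 1.0 × 0.7 × 0.2 = 0.14 SD | 7.0% | 4.5% |
| 1.0 SD | 50% | 1.0 × 0.7 × 0.4 = 0.28 SD | 15.5% | 4.6% |

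Adding the term brought the mean bias to about zero. With use at 20% among females in every group there was no bias, and the error rate was about 5% with or without the term.

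**Step 4. Form of the adjustment.** The hypothesis is tested by time × group. A contraceptive main effect shifts a user's level equally at all times and leaves that interaction unadjusted. The term must therefore be crossed with time. With three time levels this costs 1 between-subject df and 1 × (3 − 1) = 2 within-subject df.

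**The case against.** **The adjustment is promised, and the covariate list may simply be incomplete.** Physiological consistency of measurement links control of oral contraceptives to cortisol, and the hormone paragraph does not say that its list is exhaustive. This stands in part: a reader might infer that the sponsor has decided on an unadjusted analysis, and the documents do not show that. But the covariate lists are specific and vary by outcome, and medication is named for some models and not for this one. The text is contradictory, and followed as written the hormone paragraph leaves the confounder in. Nor is this detail that an article leaves to a fuller plan, because the article does state the covariates.

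**Direction and existence of bias are unknown.** This stands. A reader might infer that the omission favours the hypothesis. That needs higher use in patients, and no section gives use by group.

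**The upper figure is extreme.** This also stands. A whole-sample difference of 0.3 would need 0.3 / 0.7 ≈ 0.43 among females if 70% are female, in participants aged 12 to 17, and it is paired with the largest assumed blunting. It is also tempting to express the bias as a share of the effect the study is sized to detect. Sample size and power analysis does not state the effect size entered, and it argues from connectivity studies, so it offers no benchmark for hormones.

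**The evidence cited concerns cortisol only.** Correct. The documents show no contraceptive effect on OXT or sAA.

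**Table 1 may describe recruitment.** Its phrase "school type, handedness, pubertal status, contraceptive intake are controlled for" stands beside the matching rule and need not mean a model term. The point therefore rests on the other two sections. For the same reason, the absence of school type from every model does not show a missing covariate.

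**A yes/no medication term would do little.** This is fair. Medication is nearly nested in the patient groups, so the term would be estimated mainly within them and could not cleanly separate drug from disease against controls. Leaving it out of the primary hormone model is defensible; leaving the general promise to correct for it unexplained is not.

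**Conclusion.** The point holds as an internal contradiction with a conditional consequence. Two sections promise control of contraceptive use, one of them because of its effect on cortisol; the primary hormone model and every other model omit it. The primary CORT comparison is biased if use differs between patients and controls beyond what sex, age and pubertal status explain, in either direction. The size cannot be determined from the documents. Under the assumed inputs it is 0.05 to 0.30 SD, and in the simplified simulation the type I error rises from a nominal 5% to between 5.8% and 15.5%; with balanced use both problems vanish. The contradiction itself depends on none of these assumptions.

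For psychotropic medication the finding is narrower: Eligibility criteria promises a correction that the hormone analysis does not describe, and a simple covariate would not deliver it for the comparison with controls.

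**What to change.** Make these changes before the hormone data are analysed:

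1. In Primary outcomes, add hormonal-contraceptive use (yes/no) and its interaction with time to the repeated-measures hormone models, and add it as a covariate in the AUC and delta-score models. This is essential for CORT; apply it to OXT and sAA for consistency.
2. Add a sensitivity analysis that compares unmedicated patients with controls on the hormone outcomes.
3. Reword Eligibility criteria so that it states how psychotropic medication is handled in the hormone analysis.

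Both variables are already to be recorded, so no new data are needed. The cost is 1 between-subject df, 2 within-subject df for the interaction with a three-level time factor, and one sensitivity analysis in a smaller and therefore less precise sample.
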